### Community-based collaboration

Our study is consistent with the community engagement research framework whereby researchers engage communities in study and intervention development and implementation planning (e.g., [37]). Most community engaged research on mental health treatment has been conducted in urban settings without attention to the translational aspects of such interventions to rural communities (e.g., [38–40]). The current community-based research study was developed through a collaborative process involving researchers, Federal HV Program site leaders, and State-level Maternal and Child Health administrative leaders. We identified an efficient way to integrate home visitor training into standard HV program operations since the study’s training aligns with a national HV benchmark [1] that pertains to maternal depression. We developed a study implementation plan and ensured that home visitor study responsibilities would not interfere with their job responsibilities.

Furthermore, we conducted a preliminary small research study that produced findings that suggested a need to integrate the video-based, family-oriented treatment into the two Federal HV Program sites. Its purpose was to explore home visitor interest in supporting adolescent mothers’ mental health treatment and to explore family attitudes towards video-based family mental health treatment. Home visitors, mothers, and family members were recruited from September 2016 through December 2016. Home visitors, mothers, and their family members anonymously completed web-based surveys on a secure, password-protected website. Five home visitors, six adolescents, and three of their family members completed the surveys. For the home visitor survey, we adapted items from a reliable and valid needs assessment [41] and added items on family support team responsibilities. For the maternal and family member surveys, we adapted items from reliable and valid treatment motivation [42] and stigma [43] scales and added items on video-based family therapy.

The results showed that all home visitors wanted to (i) learn to reinforce maternal coping skills, (ii) participate in some family therapy sessions, and (iii) talk with the family therapist weekly. They also reported that workload and outside pressures would not reduce their motivation to participate in the mother’s treatment. The results showed that adolescent mothers (i) preferred video-based treatment instead of clinic-based treatment, (ii) felt comfortable with video-based treatment, and (iii) wanted their home visitors to participate in some family therapy sessions. The results showed that their family members (i) wanted to participate in adolescent mothers’ treatment and (ii) preferred video-based treatment instead of clinic-based treatment. No family members endorsed stigma concerns. However, 33% of mothers disagreed that seeking treatment for depression was a sign of personal strength. This finding and our discussions with HV program site staff about maternal stigma attitudes informed our decision to present the study treatment to home-visited families as solution-focused, rather than problem-focused, in the current study.

## Methods/design

### Study design

The current study is a quasi-experimental, implementation-effectiveness hybrid trial. Aspects of the study align with a hybrid trial design that includes dual testing of clinical interventions and implementation strategies as described by Curran, Bauer, Mittman, Pyne, and Stetler (2012) [44]. For instance, the first and second aims pertain to implementation aspects of the design and reflect strategies to explore the feasibility and acceptability of implementing the treatment model within the Federal HV Program site service delivery system for adolescent mothers and their families. Also, the third aim pertains to clinical effectiveness aspects of the design by exploring preliminary impacts on outcomes in the context of home visiting, a real-world setting. Some aspects of this pilot study differ from the hybrid trial design described by Curran et al. (2012) [44] in that participants will not be randomized to an intervention or control group and the current study includes a matched historical comparison group with adolescent mothers who were previously enrolled in the home visiting programs.

### Setting

The video-based sessions will be delivered by a therapist in a private clinical office in a hospital. Adolescent mothers and their family members will participate in the video-based sessions from their homes using a cell phone, tablet, or computer.

### Participant selection

The two Federal HV Program sites employ a total of 10 home visitors and serve about 44 families in three counties in New England. Eight home visitors and 12 adolescent mothers (pregnant *and* post-delivery), ages 13–25 years old, and their family members (six families per site) will be recruited. “Family member” is defined as one who is biologically related to the adolescent mother or a significant close other with whom she is not biologically related. The sample size was determined in consultation with our external community stakeholders. They recommended that we implement the protocol in two different Federal HV Program sites with a small number of families (i.e., 6 per site) in order to obtain early evidence of feasibility (e.g., implementation strategies such as staff training, research strategies such as family recruitment and retention) and acceptability (e.g., perceived agency burden, family receptivity) in preparation for larger studies of potential effectiveness and scalability.

This study also includes a historical comparison comprised of 12 depressed adolescent mothers who were previously enrolled in home visiting and have similar characteristics to those who will be recruited for the study. We will match the previously enrolled adolescent mothers to intervention group mothers based on scores of the *Edinburgh Postnatal Depression Scale* (*EPDS*) [45] administered at equivalent time intervals, maternal age, home zip code, pregnancy trimester or infant age for postpartum adolescents, relationship status, average annual income, and highest level of education.

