## Background

The Federal Maternal, Infant, and Early Childhood Home Visiting (HV) Program serves about 160,000 vulnerable families at risk for child abuse throughout the USA and aims to improve several outcomes, including maternal mental health [1]. About 40% are adolescent mothers (pregnant *and* post-delivery), and over a third of adolescent and adult mothers report clinically significant peripartum depressive symptoms [2]. Untreated maternal depression can lead to dysfunctional parent-child interaction [3] and an increased risk for child maltreatment [4]. Furthermore, research has shown that relational factors, such as discomfort with trust, result in poor home visiting impacts for children of depressed mothers. For example, research has shown that home visiting did not improve cognitive development or reduce behavioral problems in children of home-visited mothers with both severe depressive symptoms and discomfort with trust [5].

The addition of depression screening and mental health service referral to HV programs does not equate to receipt of treatment for all mothers. HV programs establish agreements with community mental health centers and providers to facilitate the coordination of services for depressed mothers [6]. Home visitors are expected to screen and identify depressed mothers and to make referrals for treatment. Yet, those who are referred for treatment infrequently obtain it or do not complete it if they do obtain it [6–9]. Commonly reported barriers to mental health treatment include logistical factors (e.g., no child care, lack of transportation, geographical distance) [10] and stigma for some families [11, 12]. Thus, home-visited depressed mothers have limited access to evidence-based treatment [6].

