### Inclusion criteria for home visitors and families

Home visitors must be willing to participate in the study. Home visitors must intend to remain in their current jobs for at least 12 months. Finally, home visitors must be fluent in English since the training on study responsibilities, treatment model, implementation meetings, and supervision sessions will be carried out in this language.

Adolescent mothers, ages 13–25, in the first trimester of pregnancy through 18 months postpartum with *Edinburgh Postnatal Depression Scale* (*EPDS*) [45] scores of ≥ 8 will be recruited for study participation. At least one of the adolescent mother’s family members must be willing and available to participate in eight of the 10 video-based family therapy sessions. All families must be fluent in English and have a consistent Internet access (i.e., subscribe to an Internet service provider and do not experience weekly disruptions in service) on a cell phone or computer equipped with a camera and microphone.

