### Family exclusion criteria

Home visitors routinely screen clients for substance abuse and domestic violence. Home visitors will review adolescent mothers’ most recent substance abuse and domestic violence screening measures, and those who screen positive for substance abuse or domestic violence will be excluded from the study since the study intervention does not target these types of problems. Adolescent mothers who report or exhibit current suicidal ideation, self-injurious behavior, and psychotic symptoms during a recent home visit or in a study treatment session will be excluded from the study as these symptoms require more intense treatment than what is offered in the current study. Adolescent mothers who report homicidal ideation to the home visitor or study therapist will also be excluded from the study. Similarly, those experiencing severe major depressive episodes will be excluded since they would require more intense treatment. If adolescent mothers develop more severe depressive symptoms during the course of the study, then they will receive expedited referrals for intensive psychopharmacological and psychotherapeutic treatments. Families with current Child Protective Service involvement will be excluded because they will not be enrolled in the child abuse prevention home visiting program sites from which we are recruiting participants for the current study. Research assistants will ask families if they are currently or have previously received dialectical behavior therapy (DBT) and if they are currently receiving family therapy. Families who report that they are currently or have received DBT will be excluded as the study intervention may conflict with their existing treatment, and previous exposure to DBT will confound our results for the current study. Similarly, families who report current family therapy involvement to the study therapist will be excluded to prevent a potential conflict with their existing treatment.

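### The historical comparison mothers are matched on seven variables but never screened against the trial's own eligibility criteria, so the EPDS comparison is open to selection bias

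*Protocol article*

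**What the plan says.** Under Participant selection, the article describes "a historical comparison comprised of 12 depressed adolescent mothers who were previously enrolled in home visiting and have similar characteristics" to those of the recruited mothers. It then says what the matching rests on: EPDS scores "administered at equivalent time intervals, maternal age, home zip code, pregnancy trimester or infant age for postpartum adolescents, relationship status", followed by "average annual income, and highest level of education". That makes seven variables.

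The treated mothers pass through a longer filter. Under Family exclusion criteria, "those who screen positive for substance abuse or domestic violence will be excluded from the study". The same section excludes mothers with suicidal ideation, self-injury or psychotic symptoms, whether seen at a home visit or in a study treatment session. It also excludes homicidal ideation, severe major depressive episodes, current or past DBT and current family therapy. Under Inclusion criteria, at least one of the mother's "family members must be willing and available to participate in eight of the 10" sessions.

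Under Planned analyses (third aim), EPDS change is compared between the groups at six months after enrolment in home visiting, and significantly lower EPDS in the treated mothers counts as evidence of effectiveness. The Discussion and Limitations say that the pilot is not powered for statistical differences and is not meant to test impact. The Limitations acknowledge the lack of randomisation but not the unequal eligibility of the two groups.

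**The concern.** A historical control group is informative only if its members could have entered the trial. Here the article states the selection rule, and followed as written it allows into the comparison group mothers whom the trial would have turned away.

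The article's own reasoning makes these differences prognostic. It excludes suicidal ideation, self-injury, psychosis and severe episodes because they need more intense treatment than the study offers. It says prior DBT would confound the results, but asks only the families being recruited about it. Its Background links low family cohesion and weak parental connectedness to worsening depressive symptoms, yet only treated mothers must have a relative or close other committed to most sessions.

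At stake is whether an EPDS difference between the groups reflects the treatment or the selection. The third aim hypothesises a greater reduction in depression than in the historical group, so the result will be read as a signal of effect however the pilot is labelled.

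**Working it through.** **1. The plan's own figure.** Six mothers per site × 2 sites = 12, with 12 historical mothers. This reproduces. The basis given is "The sample size was determined in consultation with our external community stakeholders". The article states no alpha, power, effect size or SD, so there is no power calculation to check.

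**2. Eligibility set side by side.**

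| Criterion | Treated mothers | Historical mothers |
|---|---|---|
| EPDS of 8 or more | Required | Largely implied (depressed, EPDS-matched) |
| Age, perinatal stage | Required | Matched |
| No Child Protective Service involvement | Required | Largely covered, since such families are not enrolled at these sites |
| Negative substance-abuse and domestic-violence screens | Required | Not stated |
| No suicidal ideation, self-injury, psychosis | Required, also during treatment | Not stated |
| No severe major depressive episode | Required | Only indirectly, through EPDS |
| No past or current DBT, no current family therapy | Required | Not stated |
| Participating family member | Required | Not stated |

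Three of the seven matching variables (EPDS, age, perinatal stage) are inclusion variables. None is an exclusion criterion or the family-member requirement.

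**3. Direction.** Three differences probably favour the treated group: unscreened substance abuse, violence or severe symptoms among historical mothers; the family-member requirement; and removal of treated mothers whose symptoms emerge in a session. Two points work against that. Matching on EPDS removes part of any severity gap, and historical mothers may have had DBT or family therapy, which could improve their scores.

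**4. Size, as illustration only.** Neither input is in the article. Assume that a share *p* of historical mothers would have been excluded and that they score *d* EPDS points worse at six months. Bias = *p* × *d*. Assume also SD 5, 12 per group and two-sided 0.05, so SE = 5 × √(2/12) = 2.04. With no treatment effect, the chance of a significant result favouring treatment is Φ(bias/SE − 1.96).

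| *p* | *d* | Bias | Chance of false significance favouring treatment |
|---|---|---|---|
| 0 | – | 0 | 2.5% |
| 0.10 | 2 | 0.2 | 3.1% |
| 0.20 | 4 | 0.8 | 5.8% |
| 0.40 | 6 | 2.4 | 21.6% |

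For scale, the difference detectable with 80% power is (1.96 + 0.84) × SD × √(2/12), which is about 4.6, 5.7 and 6.9 points for SD 4, 5 and 6.

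**5. How tight can the matching be?** The sites "serve about 44 families in three counties in New England". The Background gives programme-wide figures: about 40% of clients are adolescent mothers, and "over a third of adolescent and adult mothers report clinically significant peripartum depressive symptoms". Then 44 × 0.40 × 1/3 = 5.9 candidates at one time. An assumed upper end, with all clients adolescent and half depressed, is 44 × 1.0 × 0.5 = 22. The size of the historical pool is not stated. Suppose each variable is cut to only two levels, evenly spread and independent: 2⁷ = 128 cells. The expected number of the 12 treated mothers with an exact match in a pool of *N* is 12 × [1 − (127/128)^*N*]:

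- *N* = 6: 0.55
- *N* = 30: 2.5
- *N* = 60: 4.5
- *N* = 120: 7.3

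Real variables are correlated, so this is only indicative. It suggests that close agreement on all seven is unlikely and that some variables will have to give way.

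**The case against.** The strongest reply is that this is an exploratory comparison in an unpowered pilot, that the article says results will not test impact, and that a condensed article may leave matching detail to the full protocol. Calipers, the algorithm and who makes the match are indeed such detail, and their absence is not the point here. The selection rule itself is stated, however, and the third aim still attaches evidence of effectiveness to the comparison.

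Four stronger readings are tempting, and the article does not support them.

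- **That the seven variables cannot all be matched.** The article does not require exact or one-to-one matching, and frequency or distance matching would fit its wording. The pool is unstated, and applying programme-wide rates to these sites gives about 6 candidates at a time, which sits awkwardly with a plan to recruit 12.
- **That the comparison is shown to favour treatment.** That is the likely direction, but there are forces the other way.
- **That historical mothers might be picked with their follow-up scores in view.** Nothing in the text suggests this.
- **That EPDS is matched at follow-up as well as baseline.** The natural reading of the equivalent-intervals phrase concerns when the EPDS was given, and matching on the six-month score would defeat the stated comparison by pulling the difference towards zero. The wording does not rule it out, so a clarifying sentence is worthwhile, but it is not evidence of an error.

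It is also fair that the Child Protective Service and EPDS thresholds are already largely met in the historical group.

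**Conclusion.** The point holds in this form: the historical mothers are chosen without the trial's exclusions or its family-member requirement, so the two groups differ in eligibility on factors that the article itself treats as prognostic. The six-month EPDS comparison is open to selection bias, probably but not certainly in favour of the treated group.

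The size cannot be computed, because the article gives neither the share of past clients who would have been excluded nor their EPDS course. The 0.2 to 2.4 points, and the corresponding 3% to 22% chance of false significance, rest wholly on the assumptions shown. Even the upper figure is below the smallest difference that 12 per group could reliably detect (4.6 points at SD 4). The issue is therefore how the comparison is interpreted; the feasibility and acceptability aims are untouched. The change is worth making because it is cheap and acknowledging non-randomisation does not cover it.

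**What to change.** 1. Before matching, restrict the historical records to mothers who meet the trial's criteria as far as site records can show: at least negative substance-abuse and domestic-violence screens, and no recorded suicidal ideation, self-injury or psychosis. The article says the substance-abuse and violence screens are routine, so they may already be on file.
2. State that matching uses only the pre-treatment (qualifying) EPDS, not the six-month score that is the outcome.
3. Give baseline EPDS and perinatal stage priority, and let the other five variables be matched as closely as the records allow.
4. Add to the Limitations that family engagement and exclusion during treatment have no counterpart in the historical group.

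The cost is some chart review and a few sentences of protocol text. Fewer historical mothers may qualify, possibly fewer than 12, and matching on the remaining variables will be looser. Family engagement cannot be reproduced from records and will remain a difference between the groups.

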### Inclusion criteria for home visitors and families

Home visitors must be willing to participate in the study. Home visitors must intend to remain in their current jobs for at least 12 months. Finally, home visitors must be fluent in English since the training on study responsibilities, treatment model, implementation meetings, and supervision sessions will be carried out in this language.

Adolescent mothers, ages 13–25, in the first trimester of pregnancy through 18 months postpartum with *Edinburgh Postnatal Depression Scale* (*EPDS*) [45] scores of ≥ 8 will be recruited for study participation. At least one of the adolescent mother’s family members must be willing and available to participate in eight of the 10 video-based family therapy sessions. All families must be fluent in English and have a consistent Internet access (i.e., subscribe to an Internet service provider and do not experience weekly disruptions in service) on a cell phone or computer equipped with a camera and microphone.

### Family exclusion criteria

Home visitors routinely screen clients for substance abuse and domestic violence. Home visitors will review adolescent mothers’ most recent substance abuse and domestic violence screening measures, and those who screen positive for substance abuse or domestic violence will be excluded from the study since the study intervention does not target these types of problems. Adolescent mothers who report or exhibit current suicidal ideation, self-injurious behavior, and psychotic symptoms during a recent home visit or in a study treatment session will be excluded from the study as these symptoms require more intense treatment than what is offered in the current study. Adolescent mothers who report homicidal ideation to the home visitor or study therapist will also be excluded from the study. Similarly, those experiencing severe major depressive episodes will be excluded since they would require more intense treatment. If adolescent mothers develop more severe depressive symptoms during the course of the study, then they will receive expedited referrals for intensive psychopharmacological and psychotherapeutic treatments. Families with current Child Protective Service involvement will be excluded because they will not be enrolled in the child abuse prevention home visiting program sites from which we are recruiting participants for the current study. Research assistants will ask families if they are currently or have previously received dialectical behavior therapy (DBT) and if they are currently receiving family therapy. Families who report that they are currently or have received DBT will be excluded as the study intervention may conflict with their existing treatment, and previous exposure to DBT will confound our results for the current study. Similarly, families who report current family therapy involvement to the study therapist will be excluded to prevent a potential conflict with their existing treatment.

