^d^Monitoring measures completed at the end of therapy sessions 4 and 8; diagnostic interviews will only be used for adolescent mothers with increased BDI-II scores

Study measures will be completed at three time points: home visitor baseline (O_1_), family baseline and treatment (O_2_), post-treatment and the 2-month follow-up (O_3_). Home visitor baseline measures will include demographic information (age, level of education, and tenure) and turnover intention within 12 months. For knowledge of HIPAA-compliant video-based communication technology, home visitors will demonstrate its use on their laptops and cell phones. For knowledge of family eligibility/inclusion and exclusion criteria, co-investigators will monitor home visitor identification of eligible families, record discrepancies and resolutions, and record the percent of eligible families recruited. Family baseline measures will be completed in O_2_, within 2 weeks prior to the first therapy session. Demographic information will be collected on adolescent mothers, infants (age only), and family members. Monitoring measures will be completed in O_2_. Home visitor post-treatment measures (completed within a month of their last family completing treatment), family post-treatment measures (completed at the end of the final therapy session), and the 2-month family follow-up will be completed in O_3_.

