
For the second aim, univariate statistics (e.g., means, proportions, 95% confidence intervals) will be used to characterize family baseline characteristics and indicators of feasibility (quality of delivery and retention). Bivariate statistics will be used to explore the associations of family baseline characteristics with indicators of feasibility. For quality of delivery, average therapist scores and family scores will be calculated for each subscale on the *Working Alliance Inventory-Short Revised* (Therapist and Client versions—see Table 1) [49, 50] after family therapy sessions 6 and 10. High quality of delivery will be determined by *Working Alliance Inventory-Short Revised* Therapist and Client mean scores of 5 and above on each subscale at post-treatment. For retention, the total number of attended family therapy sessions will be calculated. Ratios for the actual to expected number of family therapy sessions will be calculated. High retention will be evidenced by families attending 70% of the expected number of sessions. For acceptability (family responsiveness), univariate statistics and qualitative data analytic methods [47] will be used. For family completion of homework assignments, the percentage of completed assignments will be calculated overall and for each coping skill module. Family completion of one homework assignment per coping skill module will suggest the treatment is acceptable to families. For family satisfaction, averages will be calculated for multiple-choice items and three independent experienced coders will code responses to the open-ended questions [47]. A thematic analytic approach [48] will be used due to the semi-structured, open-ended questions on the satisfaction questionnaire. The independent coders will use traditional open coding for the open-ended questions and free text responses. Thematic analysis will be conducted using inductive coding [48]. The independent coders will schedule consensus meetings to discuss codes and resolve discrepancies. Codes will be grouped into categories to create themes, which will be identified through consensus. The emergent themes will be identified and summarized [47].

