For the third aim, the internal consistency of each outcome measure will be assessed. Basic sample statistics (e.g., means, proportions, 95% confidence intervals) will be used to characterize family baseline, post-treatment, and follow-up measures. Difference scores will be calculated, and treatment impacts on outcomes will be explored from baseline to post-treatment to follow-up. Evidence of effectiveness will be demonstrated at follow-up by significant reductions in depressive symptoms and emotional suppression, and significant improvements in cognitive reappraisal, parental empathy, and family functioning. We will compare changes in *EPDS* scores of previously enrolled adolescent mothers to those of adolescent mothers who received the study treatment at 6 months post-enrollment in the HV program. Evidence of effectiveness will be demonstrated by significantly lower *EPDS* scores in adolescent mothers who received the study treatment.

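### Exclusion criteria are applied after treatment has started, to events related to the depression outcome; dropping these mothers would tilt the Aim 3 depression results toward the treatment

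*Protocol article*

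**What the plan says.** All references are to the protocol article.

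**Family exclusion criteria.** Mothers with suicidal ideation, self-injury or psychotic symptoms "during a recent home visit or in a study treatment session will be excluded from the study". A second sentence reads: "Adolescent mothers who report homicidal ideation to the home visitor or study therapist will also be excluded from the study". A third says that "those experiencing severe major depressive episodes will be excluded since they would require more intense treatment", and gives no time point. The sentence after it reads: "If adolescent mothers develop more severe depressive symptoms during the course of the study, then they will receive expedited referrals". It does not say whether such a mother stays in the study.

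**Study measures, Table 1 and its notes.** The BDI-II is repeated at the end of sessions 4 and 8, and "diagnostic interviews will only be used for adolescent mothers with increased BDI-II scores". Family post-treatment measures are taken at the end of the last session.

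**Study purpose and aims; Planned analyses.** The hypothesis and the Aim 3 analysis both set mothers who received the treatment against previously enrolled mothers. Effectiveness is to be shown by significantly lower EPDS scores in "adolescent mothers who received the study treatment". The article does not define who counts as having received it.

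**Participant selection.** Twelve historical mothers are matched on EPDS scores at equivalent intervals and on demographic and pregnancy factors. No removal for later events is stated for them.

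**Feasibility criteria.** The aims ask for retention of at least 80% of families, and Table 1 measures the percentage completing treatment. High quality of delivery is defined by Working Alliance Inventory "mean scores of 5 and above on each subscale at post-treatment", although averages are also calculated after session 6.

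**The concern.** An exclusion criterion normally decides who enters. Here part of the list operates on mothers who have consented, completed baseline measures and begun therapy, and the stated consequence is leaving the study, not only stopping the study treatment. The triggering events are related to the course of depression, so the mothers removed would tend to be those doing badly. If they are removed from the intervention group while the historical group keeps its own poor outcomes, the intervention group looks better even when the treatment does nothing.

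At stake are the within-group depression change and the EPDS comparison in Aim 3. Depending on how the denominator is handled, the 80% retention target could also be affected. With 12 mothers, one or two removals matter.

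**Working it through.** The article gives no power, alpha, effect size, SD or drop-out figure, and the group size was set with community stakeholders. There is no planned figure to reproduce. The check has three parts.

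**1. Which events remove a mother after enrolment**

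- Suicidal ideation, self-injury or psychotic symptoms seen in a treatment session: exclusion, necessarily after therapy has begun.
- Homicidal ideation told to the study therapist: exclusion, and this can occur after enrolment.
- Severe major depressive episode: exclusion, timing not given.
- More severe depressive symptoms during the study: referral only, as far as the text goes.

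The last two do not say what happens when a severe episode arises during therapy. The diagnostic interviews are reserved for mothers with increased BDI-II scores, which makes that case a foreseeable one.

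**2. Effect on the EPDS comparison (illustration)**

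From the article: 12 intervention and 12 historical mothers. Assumed: no true effect; standardised normal EPDS change; an unpaired t-test, two-sided at 0.05 (the article names no test or alpha); 1 to 3 mothers dropped from the intervention group only.

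Each intervention mother has a clinical course u, and her outcome is x = ρu + √(1 − ρ²)·e, with u and e independent standard normal. The k mothers with the worst u are dropped, and the remaining 12 − k are compared with 12 historical mothers. There were 100,000 simulated trials per row.

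| Dropped (k) | Shift, ρ = 1.0 | P(significant, favours treatment), ρ = 1.0 | Shift, ρ = 0.5 | P(significant, favours treatment), ρ = 0.5 |
|---|---|---|---|---|
| 0 | about 0 | 2.6% | about 0 | 2.4% |
| 1 | 0.148 SD | 6.1% | 0.076 SD | 3.8% |
| 2 | 0.275 SD | 10.6% | 0.135 SD | 5.1% |
| 3 | 0.394 SD | 16.2% | 0.195 SD | 6.5% |

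With nobody dropped, the chance is the nominal one-sided 2.5%, within simulation error. All shifts favour the treatment.

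**3. Retention, if excluded mothers left the denominator**

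The target is 0.80 × 12 = 9.6, so 10 of 12 families must complete.

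- 9 completers, all 12 counted: 9/12 = 75.0%, target missed.
- 9 completers, one excluded mother taken out: 9/(12 − 1) = 9/11 = 81.8%, target met.
- 8 completers, all 12 counted: 8/12 = 66.7%, target missed.
- 8 completers, two taken out: 8/(12 − 2) = 8/10 = 80.0%, target met.

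This shows only what the choice of denominator would do. The article does not say which denominator applies.

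**The case against.** The best defence is that this is a small pilot about feasibility and acceptability. The Discussion says it is not powered to test differences, and the Limitations say its results will not be used to test impact. The phrase about mothers who received treatment may do no more than tell the intervention group apart from the historical one, and analysis sets are commonly left to a fuller document. EPDS screening is routine home-visitor practice and home visiting does not depend on study participation, so a 6-month score could exist for an excluded mother. Nothing says it would be discarded.

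Much of this stands, and it limits the point. A reader might infer several stronger things that the article does not support:

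- **That any mother who worsens is removed.** Rising depressive symptoms lead to a stated referral. Exclusion is stated for the specific events listed above.
- **That retention is inflated.** No sentence takes excluded mothers out of the denominator. Counted as non-completers, they lower retention.
- **That alliance results are inflated.** Post-treatment scores would be missing, but session 6 averages are planned, and disclosing such symptoms to a therapist does not imply a poor alliance. The direction of any bias is unknown.
- **That every exclusion reported to the therapist is outcome-related.** The rule that "families who report current family therapy involvement to the study therapist will be excluded" concerns concurrent treatment.
- **That a safety signal is hidden.** Monitoring and referral are described, and nothing says these events go unreported.

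The defence does not remove the core. Exclusion from the study after a treatment-session event is stated text, not a detail left for later. The Planned analyses also set a significance standard for EPDS despite the pilot disclaimers. A small sample explains imprecision; it does not excuse selective removal.

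**Conclusion.** The concern holds for Aim 3. As written, the article excludes enrolled mothers from the study for acute events related to depression, and states no equivalent removal for the historical group. If those mothers drop out of the analysis, the depression change and the EPDS comparison are biased in favour of treatment.

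The size is illustrative. Across 1 to 3 removals and correlations of 0.5 to 1.0, the bias is about 0.08 to 0.39 SD, and the false-positive chance in favour of treatment rises from about 2.5% to between 3.8% and 16.2%. The article gives no rate for these events, no EPDS standard deviation and no correlation, so the lower end is as admissible as the upper. The result also assumes that the historical group is not subject to the same removals, on which the article is silent.

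Retention is a conditional risk only, and alliance is a missing-data matter without a known direction. Separately, the sentences on severe episodes and on symptoms that become more severe during the study must be reconciled.

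**What to change.** Leave the clinical rule for moving a mother to other care unchanged, and separate it from the analysis.

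1. Use the criteria as study exclusions only before the first therapy session. Record later events as discontinuation of study treatment.
2. State whether a severe episode arising during therapy falls under the exclusion sentence or the referral sentence.
3. Define who counts as having received the treatment. Keep all enrolled mothers in the EPDS comparison, and in the Aim 3 post-treatment and 2-month follow-up where they agree.
4. Keep all enrolled families in the retention denominator, counting those who discontinue as non-completers.
5. Report the number of such mothers and the reasons.
6. Report session 6 alliance scores for families without a session 10 score.

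The cost is a wording change and follow-up questionnaires for a few mothers. EPDS is already part of routine home-visitor screening, so that score should need little extra work for mothers who remain in home visiting. The results may look less favourable.
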